# Feasibility and preliminary effects of a mindfulness-based physical exercise (MBPE) program for community-dwelling older people with sarcopenia: A protocol for a parallel, two-armed pilot randomised controlled trial

**DOI:** 10.1371/journal.pone.0302235

**Published:** 2024-04-18

## Abstract

**Introduction:**

Physical exercise (PE) is essential for alleviating the symptoms of sarcopenia. Low motivation is a major barrier to PE. Mindfulness-based intervention (MBI) has the potential to improve motivation. However, few studies have used a mindfulness-based PE (MBPE) intervention among older people with sarcopenia.

**Objectives:**

To assess the feasibility, acceptability and preliminary effects of the MBPE program among community-dwelling older people with sarcopenia.

**Methods and analysis:**

A two-arm pilot randomised controlled trial will be conducted to assess the feasibility, acceptability and preliminary effects of an MBPE program among community-dwelling older people with sarcopenia. A total of 60 participants will be randomised into the intervention group, receiving the MBPE intervention twice a week over 12 weeks, or the control group, receiving health education with the same duration, number of sessions and frequency as the intervention group. Each session of the MBPE program will last about 60 min, including 5-10- min introduction, 20-min MBI, 30-min PE and 5-10-min sharing and discussion. The primary outcomes will be the feasibility (i.e., the time spent recruiting participants, the eligibility rate and the recruitment rate) and acceptability (i.e., the attendance rate, completion rate and attrition rate) of the MBPE program. The secondary outcomes will be the preliminary effects of the MBPE program on symptoms of sarcopenia, motivation for PE, psychological well-being, mindfulness level, physical activity level and quality of life. Individual interviews will be conducted to identify the strengths, limitations and therapeutic components of the intervention. The quantitative data will be analysed by generalised estimating equations. The qualitative data will be analysed by Braun and Clarke’s thematic approach.

**Conclusion:**

The findings of this study will be able to provide evidence for the health professionals in adopting MBPE as a supportive intervention for the older adults with sarcopenia and the groundworks for the researchers in developing non-pharmacological intervention for older adults. The positive effects could facilitate healthy ageing and relief the burden of the medical system, especially in the countries facing the ageing population.

**Trial registration number:**

NCT05982067; ClinicalTrials.gov.

## Introduction

Sarcopenia is a progressive and generalised skeletal muscle disorder characterised by decreased muscle mass, muscle strength and physical function [1]. It is classified as an independent disease with the code ICD-10-CM (M62.84) by the World Health Organization [2]. Globally, it is estimated that over 120 million older adults are living with sarcopenia, and this number is expected to double by 2050 [3, 4]. Compared with healthy ageing, sarcopenia significantly increases the risks of various adverse health events, such as falling by 3.23 times, fracture by up to 3.75 times [5], hospitalisation by 2.07 times [6] and all-cause mortality by 2.20 times [7] and it is also negatively associated with psychological well-being [8]. Sarcopenia greatly increases healthcare costs and burden in medical system [9]. Thus, it is imperative to find a way to manage sarcopenia in order to promote healthy ageing worldwide.

Currently, there are no approved medications for treating sarcopenia [10]. Lifestyle interventions, especially physical exercise (PE) interventions, have been demonstrated to mitigate the symptoms of sarcopenia [11–15]. Thus, PE is strongly recommended as the first-line treatment [16]. However, the low adherence and motivation to regular PE is a major concern in older adults with sarcopenia [17]. A systematic review (SR) demonstrated that the adherence to PE interventions by healthy older adults was approximately 60% [18]. The adherence of older adults with sarcopenia might be even lower than 60% due to their decreased physical function, PE ability and mobility [19]. This problem has been extensively investigated in numerous prior studies [20–23], but effective interventions and management have not been adequately addressed or explored in the existing literature.

Distraction, mind-wandering and negative thoughts and feelings, such as fatigue, anxious or hopeless during the PE, were the common barriers affecting the motivation among the older adults with sarcopenia in performing PE, in addition to physical function and supervision [24, 25]. For example, study has indicated that older adults with sarcopenia are easily derailed by issues in daily life [26] and misled by their preconceived misunderstandings about PE, such as the belief that they are too old to perform any kind of PE [20]. The PRIME (Plans, Impulses, Inhibitions, Motivations, Evaluations and Response) theory of motivation (S1 Fig, details in Conceptual framework of the MBPE program section) explained diversity of factors that influence motivation and emphasized the positive feelings and non-judgmental self-awareness for engaging people in goal-directed behaviour [25, 27]. Although prior studies adopted various strategies to improve adherence and motivation to PE for the older adults with sarcopenia [12], only a few of them took these components (e.g., distraction, negative feelings) into consideration when designing the PE program. Moreover, as the above negative feelings and experiences of older adults with sarcopenia regarding PE are also likely to undermine their psychological well-being and may lead to mental health issues (e.g., anxiety, depression) [28]. Therefore, a way to promote the positive feelings and non-judgmental self-awareness to enhance their motivation in performing PE and ultimately improve their physical health as well as psychological well-being is urgently required.

Mindfulness is defined as a process of openly attending with awareness to one’s present moment [29]. Mindfulness-based intervention (BMI) is primarily designed for treating depression and other mental health problems [30, 31]. Additionally, an increasing number of studies have demonstrated its positive effects in enhancing the PE levels in different populations [32–34]. One SR [35] concluded that MBIs effectively activated the motivation to perform PE and the adherence to PE in older adults, and a 4-week RCT [36] reached a similar conclusion. Moreover, the adherence to MBI can be maintained even after the program has ended [37]. The mindful coping model (S2 Fig) offers a possible explanation of the positive effects in which the MBI direct the participants’ attention away from their negative thinking, enhance their engagement in the daily activities and PE and evoking positive feelings [38]. This implies that MBIs could be incorporated into PE interventions to improve both the adherence to PE and the psychological well-being of older adults with sarcopenia.

However, despite the benefits of MBIs, few studies of mindfulness embedded into PE interventions for older adults with sarcopenia older people have been conducted. To the best of our knowledge, only two mindfulness-based PE interventions (MBPE) have been conducted in this population, adopting mindful yoga education [39] and Tai Chi [40]. However, limitations exist in these two studies, focusing solely on women [39] or solely on men aged 85 years or older [40], not assessing muscle mass [39, 40], even though muscle loss is a key symptom of sarcopenia. Importantly, neither of these studies included resistance exercise, which is the most highly recommended type of PE to treat sarcopenia [16]. It is imperative to develop a novel intervention combining MBI and PE (specifically resistance exercise) to activate and improve the motivation for and adherence to PE, mitigate sarcopenia and improve psychological well-being in older adults with sarcopenia. Given the limited evidence in this field, this pilot RCT aims to explore the feasibility, acceptability and preliminary effects of a MBPE intervention in community-dwelling older people with sarcopenia.

### Objectives and hypothesis

The objectives of this pilot RCT are as follows: (1) to assess the feasibility and acceptability of the MBPE program among community-dwelling older people with sarcopenia; and (2) to investigate the preliminary effects of the MBPE program on the symptoms of sarcopenia, motivation for PE, psychological well-being, mindfulness level, physical activity level and quality of life among this population.

We hypothesise that the MBPE program is acceptable and feasible with the potential to improve the motivation, adherence to PE, physical and psychological health of the older adults with sarcopenia.

## Methods and analysis

### Study design

This study will adopt a two-arm pilot RCT design with nested individual interviews. The Standard Protocol Items: Recommendations for Interventional Trials (SPIRIT) guideline [41] is followed in this proposal (Fig 1 and S1–S3 Appendices). The overall flow of the pilot RCT in the form of a Consolidated Standards of Reporting Trials (CONSORT) diagram is shown in Fig 2 [42]. The conceptual framework of this study is shown in Fig 3.

**Fig 1 pone.0302235.g001:**
[figure not shown]
The SPIRIT flow of the mindfulness-based physical exercise program.

**Fig 2 pone.0302235.g002:**
[figure not shown]
CONSOROT diagram of the mindfulness-based physical exercise program.

**Fig 3 pone.0302235.g003:**
[figure not shown]
The conceptual framework of the mindfulness-based physical exercise program.

### Study setting

Participants will be recruited from three community health care centres (CHCCs) in Suzhou, Jiangsu province, China. The MBPE intervention will be conducted at one of the CHCCs and at participants’ homes.

### Eligibility criteria

This study will focus on community-dwelling older people with sarcopenia. The detailed inclusion and exclusion criteria are given in Table 1.

**Table 1 pone.0302235.t001:** Eligibility criteria for participants.

**Inclusion criteria**
1. Community-dwelling and aged 60 years or older.
2. Diagnosed with sarcopenia according to the criteria of the Asian Working Group for Sarcopenia (AWGS) [43]: a) decreased muscle strength: handgrip strength of men < 28 kg; handgrip strength of women < 18 kg; b) or decreased physical performance: 5-time chair-stand test time ≥12 s; c) or decreased muscle mass: skeletal muscle mass index (SMI) of men < 7.0 kg/m^2^; SMI of women < 5.7 kg/m^2^.
3. Able to communicate orally and in writing and understand instructions.
**Exclusion criteria**
1. Hospitalisation lasting for more than 5 days in the 3 months prior to recruitment.
2. Unable to undergo body composition test, due to having a heart pacemaker, vascular stent, steel plates or other materials in the body.
3. Contraindications to PE, such as severe musculoskeletal disorders, severe cardiovascular diseases or spinal nerve injury.
4. Already undertaking regular PE: 150 min of moderate-intensity activity or 75 min of vigorous-intensity activity per week in the 3 months prior to recruitment [44].
5. Practising mindfulness/yoga for >45 min a week in the 6 months prior to recruitment [45].

### Sample size

25 per group will provide sufficient information for planning the proposed subsequent main randomised trial with an anticipated standardised effect size of about 0.2 on the primary outcome, handgrip strength [46]. Considering a 20% attrition rate [47], the sample size of this pilot RCT has been calculated as 25 × (1 + 20%) = 30 in each group.

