### Allocation and blinding

After they give their informed consent, eligible participants will be randomised into the intervention group (IG) or the control group (CG) with a 1:1 ratio. Block randomisation with a block size of 4 will be used to balance the numbers in each group. Three research assistants who will not otherwise be involved in this study will perform the randomisation independently to ensure allocation concealment and avoid selection bias. The random numbers will be generated by a computer and sealed in opaque envelopes and delivered to each participant.

Due to the characteristics of the interventions (the MBPE vs health education), it will be impossible to blind the participants and interventionists. The following personnel will, however, be blinded: the research assistants recruiting participants, the research assistants performing randomisation and the outcome assessor.

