#### 2. Acceptability of the MBPE program

Acceptability will be evaluated using the prospective acceptability, the concurrent acceptability and the retrospective acceptability [56]. Prospective acceptability will be measured as the recruitment rate and the reasons for which older adults did not get involved in the program[56]. Concurrent acceptability will be assessed using the attendance rate (sessions attended by the participants / all sessions), completion rate (sessions in which participants were actually involved and at least 80% completed / all attended sessions), attrition rate (number of participants dropping out / total number of participants) and the reasons for discontinuing [56]. Attrition will be considered if the completion rate is less than 80%. To have a depth exploration of the participants’ experience and avoid leaking privacy, individual interviews will be used to measure the retrospective acceptability, the detailed guideline in Table 3. The individual interviews will be conducted by two researchers who both have experience in individual interviewing and are familiar with sarcopenia and mindfulness. Purposive sampling will be used, and the sample size will depend on the data duration. Reflective journals written by the interviewers will be used to avoid bias and ensure the transparency of the research process [57]. With the participants’ consent, the individual interviews will be carried out face-to-face and audio recorded.

**Table 3 pone.0302235.t003:** Guide to individual interviewing of participants in intervention group.

Number	Questions
**Q1**	**Generally, what do you think of this intervention?**

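### The attrition allowance multiplies by 1.20 instead of dividing by 0.80, so 30 per group leaves an expected 24, not the 25 the plan calls sufficient

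*Protocol article*

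**What the plan says.** The Sample size section of the protocol article sets the target: "25 per group will provide sufficient information for planning the proposed subsequent main randomised trial". It links that target to "an anticipated standardised effect size of about 0.2 on the primary outcome, handgrip strength". It then allows for 20% attrition, citing a source, and states that "the sample size of this pilot RCT has been calculated as 25 × (1 + 20%) = 30 in each group".

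The Abstract (Methods and analysis) carries the result forward as the size of the trial: "A total of 60 participants will be randomised". The Allocation and blinding section sets 1:1 allocation in blocks of 4, so 60 means 30 in each group.

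The section on acceptability defines the quantity in question as "attrition rate (number of participants dropping out / total number of participants"; the denominator is therefore everyone enrolled, not those who complete.

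**The concern.** An allowance for dropout should return the number to randomise so that, once the assumed share is lost, the target remains. Multiplying the target by one plus the attrition rate does not do this when the rate is a share of those randomised. It always leaves fewer than the target, because (1 + d)(1 − d) is below 1 for any d above zero.

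What is at stake is the only justification for the trial's size that the article gives. The pilot is meant to supply means and standard deviations for planning the main trial. Outcomes are measured at baseline and immediately after the intervention only, so a participant lost before the second assessment contributes no post-intervention value. There is also a risk of carry-over: if the same formula is used for the main trial at 20% attrition, it will again retain only 1.20 × 0.80 = 96% of whatever target is set, and the shortfall in participants will grow with the size of that trial.

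**Working it through.** **Inputs**

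- Target per group, n = 25 (Sample size).
- Attrition, d = 0.20 (Sample size), as a share of all participants (definition in the acceptability section).
- Allocation 1:1 (Allocation and blinding).
- Stated size: 30 per group (Sample size), 60 in total (Abstract).

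**The plan's own figure**

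n × (1 + d) = 25 × 1.20 = 30 per group, and 2 × 30 = 60. Both stated figures reproduce exactly.

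**What 30 per group delivers at the plan's own rate**

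30 × (1 − 0.20) = 24 per group, 48 in total. This is one per group below 25, and two below 50 overall.

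**Attrition that 30 per group can absorb**

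1 − 25/30 = 0.167. Up to 16.7%, 25 remain; above it, they do not.

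**The standard allowance**

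n / (1 − d) = 25 / 0.80 = 31.25, rounded up to 32 per group, 64 in total. Check: 32 × 0.80 = 25.6, which meets 25.

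**Could the printed formula be right on another reading?**

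Multiplying by 1.20 is correct only if 20% is the number lost divided by the number completing. With 30 enrolled and 25 completing, 5/25 = 20%. The article's definition divides by the total number of participants, which gives 5/30 = 16.7%, so this reading is closed.

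**Chance of keeping at least 25**

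This assumes that each participant is retained independently with probability 0.80.

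| Randomised per group | Expected retained | At least 25 in one group | At least 25 in both groups |
|---|---|---|---|
| 30 | 24 | 0.428 | 0.428² = 0.183 |
| 32 | 25.6 | 0.698 | 0.698² = 0.487 |

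**Effect on precision**

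The approximate 95% confidence interval half-width for a standardised mean difference is 1.96 × √(2/n). With 25 per group it is 0.554; with 24 it is 0.566.

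**The case against.** The arithmetic is hard to dispute; the case on the other side is about weight, and most of it stands.

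- **Sufficient is not the same as required.** The article says that 25 per group is enough for planning. It does not say that 24 would be too few, and the figure is not derived from a power calculation. This is fair, and the error should not be described as missing a minimum.
- **The practical loss is small.** A half-width of 0.566 rather than 0.554 would change no planning decision. The article already concedes, under Strength and limitation, that a pilot has limited power and that a full trial is needed.
- **The primary outcomes are untouched.** Recruitment time, eligibility rate and recruitment rate are settled before anyone drops out, and the attrition rate is calculated on all participants. Only the secondary estimates of preliminary effect lose information.
- **Attrition may not mean missing data.** The acceptability section also counts participants with a completion rate below 80% as attrition, and such people could still attend the final assessment. An intention-to-treat analysis is planned alongside the per-protocol one. So the number with outcome data could exceed 24 at 20% attrition.
- **The probabilities need a comparator.** Even 32 per group would miss 25 in at least one arm about half the time. Much of the risk comes from planning to an expected value, not from the formula. That is why both rows appear in the table above.

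None of this makes multiplication by 1.20 correct, nor does it alter the fact that the stated size falls short of the stated number at the stated rate.

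**Conclusion.** The sample-size statement is wrong as written. At the plan's own 20% attrition, 30 per group leaves an expected 24 (48 in total) where the text implies 25 (50 in total); the allowance that matches the text is 32 per group (64 in total).

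The expected numbers rest only on the article's target, its attrition rate and its definition of attrition. Treating 24 as the number with outcome data further assumes that those counted as attrition are not measured after the intervention. The probabilities also assume independent retention.

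The consequence is modest: it does not threaten the feasibility aims or the validity of the trial. It should still be corrected, because it is a definite error in the sole justification of the trial's size and is easily repeated in the main trial.

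**What to change.** Preferred: keep 60 and correct the sentence. State that 30 per group gives an expected 24 per group remaining at 20% attrition, and that 25 per group is reached only if attrition is 16.7% or less. This costs one sentence and a slightly less favourable figure; design, recruitment and analysis do not change.

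Alternative, if 25 per group is to be held as the target: replace the formula by 25 / (1 − 0.20) = 31.25, rounded up to 32 per group, and change the total from 60 to 64 wherever it appears, including the Abstract. This costs four more participants, and 64 is 16 complete blocks of 4.

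Whichever is chosen, use division by (1 − attrition) when the main trial is sized.

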### Allocation and blinding

After they give their informed consent, eligible participants will be randomised into the intervention group (IG) or the control group (CG) with a 1:1 ratio. Block randomisation with a block size of 4 will be used to balance the numbers in each group. Three research assistants who will not otherwise be involved in this study will perform the randomisation independently to ensure allocation concealment and avoid selection bias. The random numbers will be generated by a computer and sealed in opaque envelopes and delivered to each participant.

Due to the characteristics of the interventions (the MBPE vs health education), it will be impossible to blind the participants and interventionists. The following personnel will, however, be blinded: the research assistants recruiting participants, the research assistants performing randomisation and the outcome assessor.

### Intervention development

The detailed development of the MBPE program follows the Medical Research Council (MRC) guideline for complex interventions development [48], which considered the findings from our SR [49], guidelines on PE for older adults with sarcopenia [19, 50], MBIs provided by the Oxford Mindfulness Centre [51] and Bangor University [52]. After the initail version of the MBPE program, a panel of experts including nurses, mindfulness therapist, researchers in gerontology, and geriatrician validated the protocol via a two-round Delphi process (unpublished yet). The comments and suggestions from the older adults with sarcopenia were collected to refine the MBPE protocol in this proposed study. The study will be conducted in a hybrid mode, combination of at CHCC and at home [53, 54].

### Conceptual framework of the MBPE program

Two theories, the PRIME theory of motivation (S1 Fig) and the mindful coping model (S2 Fig), was adopted to establish the conceptual framework of the MBPE program (Fig 3). Based on the mindful coping model, the mindfulness component in the MBPE program can enhance the motivation for PE by enhancing three essential elements of human motivation in the PRIME theory of motivation: focusing on the present moment, accepting of negative feelings (Self-awareness and Motives), and evoking positive feelings (Motives), which eventually maximize the benefits of PE and improve the physical health of the participants. In addition, the mindful coping model indicates that the mindfulness practice can improve the psychological health of older adults with sarcopenia.

### Intervention description

#### 1. The MBPE intervention in the IG

The MBPE intervention aims to help participants learn mindfulness and maintain the state of mindful during PE to improve their experiences of PE and motivation to perform PE [27, 38]. Each session will last for approximately 60 min and have a concrete theme, learning objectives and corresponding activities, including a 5–10-min introduction, 20-min MBI, 30-min PE and 5–10-min sharing and discussion [49, 51, 52]; details are provided in Table 2. The contents and activities of the MBI components will be adapted to the theme of each session, whereas the PE movements will be the same throughout the program but with increased intensity every two weeks until a moderate intensity (measured using the Borg scale) is achieved [50]. The MBPE intervention will be conducted twice a week for 12 weeks [19]. The content of week 8 will be repeated in weeks 9–12 to enhance the benefits of MBPE and help the participants incorporate MBPE into their daily lives, given that they are expected to be able to learn the MBI within 8 weeks [54]. To better combine the MBI and PE components, tips on remaining mindful during PE will be given to the participants.

**Table 2 pone.0302235.t002:** Themes, mindfulness and PE components in the MBPE intervention.

Week	Theme of each session	Objectives	MBI component (20 min)	PE component (40 min)
1	Introduction to MBPE	Help participants to understand mindfulness, MBPE and key points of keeping mindful	1) Mini lectures on mindfulness, MBPE and key points of remaining mindful during PE 2) Initial experience of mindfulness (3-min breath meditation)	**PE movement** 1) Warm up (10 min): mindful torso rotation, mindful shoulder rotation, mindful wrist wrap, mindful knee circles, mindful ankle rotation 2) RE (20 min): mindful lateral hand raises, mindful hip abduction, mindful bicep flexors, mindful straight leg lift, mindful handgrip strength exercise, mindful toes up, mindful heels up 3) Cool down (10 min): mindful bicep stretch, mindful tricep stretch, mindful calf stretch, mindful quadricep stretch, mindful cross-legged twist, mindful back stretch **PE intensity** 1) Fairly light (10–11 on Borg scale) 2) 2 sets, 8–10 repeats
2	Paying attention to breath during static and dynamic movements	Help participants to understand the characteristics of mindfulness and learn how to pay attention to breath	1) Mini lectures on the key characteristics of mindfulness and the importance of focusing on breath, especially for older people with sarcopenia 2) Mindful practice: 6-min breath meditation 3) Tips on paying attention to breath during PE	**PE movement** Same as Week 1 **PE intensity** Same as Week 1
3	Paying attention to body sensations during static and dynamic movements	Help participants to understand the importance of paying attention to the body and know how to do so	1) Mini lectures on body sensations and appreciation 2) Mindful practice: 10-min body scan 3) Tips on paying attention to body sensations during PE	**PE movement** Same as Week 1 **PE intensity** 1) Somewhat hard (11–12 on Borg scale) 2) 2 sets, 10–12 repeats
4	Working with pain, challenges, and stress	Help participants to learn to notice pain, challenges and stress in the body and to observe their physical limitations non-attachedly	1) Mini lecture on pain and stress, especially those that older adults with sarcopenia commonly have in daily life 2) Mindful practice of noticing and observing pain, challenges and stress: 10-min seated meditation 3) Tips on noticing physical pain, limitations, stress or challenges during PE	**PE movement** Same as Week 1 **PE intensity** Same as Week 3
5	Working with thoughts during stillness and PE	Help participants to understand the relationship between thoughts and facts and learn to notice thoughts non-judgementally	1) Mini lecture on the conditioned mind: using some common thoughts of older adults with sarcopenia to elaborate on the topic 2) Awareness of our thoughts: 7-min sitting meditation 3) Tips on noticing and dealing with thoughts during PE	**PE movement** Same as Week 1 **PE intensity** 1) Hard (12–14 on Borg scale) 2) 3 sets, 8–15 repeats
6	Understanding habitual thinking patterns during life and PE	Help participants to understand that behaviour, thoughts and feelings are interwoven, and learn to notice the tendency to label things during PE	1) Mini lectures on becoming unstuck and having a flexible mind: using common negative feelings of older adults with sarcopenia to show how these negative feelings stick in the mind, behaviour, etc. 2) Mindful practice: 7-min sitting meditation 3) Tips on observing the tendency to label things during PE	**PE movement** Same as Week 1 **PE intensity** Same as Week 5
7	Self-compassion during life and PE	Help participants to understand self-compassion, how to improve self-compassion and show more appreciation towards PE and life	1) Mini lectures on compassion vs criticism and nourishing vs depleting activities 2) Mindful practice: 7-min loving meditation 3) Tips on self-compassion during PE	**PE movement** Same as Week 1 **PE intensity** Same as Week 5
8	Mindfulness-based PE and mindfulness in life	Help participants to learn to integrate mindfulness and MBPE into daily life and to view things from a beginner’s perspective	1) Mini lecture on incorporating mindfulness and mindfulness-based PE into daily life: what informal mindfulness activities we can do in daily life; when, where and how to do formal mindfulness practice, etc. 2) Mini lecture on keeping a beginner’s mindset: its importance and how to re-view the things that we ignore or take for granted 3) Mindful practice: 7-min sitting meditation with life nourishment	**PE movement** Same as Week 1 **PE intensity** Same as Week 5

MBI, Mindfulness-Based Intervention; MBPE, Mindfulness-Based Physical Exercise; PE, Physical Exercise.

To facilitate the participants’ learning, the face-to-face sessions will be provided in the first four weeks under the supervision of a qualified mindfulness therapist and a qualified sports coach in small groups of 6–10 participants to ensure adequate supervision at the CHCC [55]. Then, the intervention sessions will gradually transition to hybrid mode during weeks 5–12. Specifically, the participants will attend the face-to-face sessions once a week in weeks 5–8 and once every two weeks in weeks 9–12. To achieve a session frequency of twice a week, in addition to the sessions at the CHCC, the participants will perform the interventions at home using videos and templates containing the MBIs and PE components of our MBPE intervention.

